## Abstract

**Background:**

The teacher’s role in school mental health initiatives cannot be overemphasized. Despite global evidence of educational interventions in improving teachers’ knowledge and attitudes regarding mental health, this area remains under researched in Pakistan. This paper presents a study protocol of a pilot randomized controlled trial to examine the effectiveness of a teacher training intervention for improving mental health literacy and self-efficacy among school teachers in urban Lahore, Pakistan.

**Methods:**

The randomized controlled trial will follow the CONSORT guidelines. Participants will be allocated to the Intervention group (receiving the World Health Organization, Eastern Mediterranean Region (WHO-EMRO) School Mental Health Manual-based intervention in three 6-h, face-to-face sessions) or a waitlist control group (not receiving training during the study period). Participants will be teachers of private schools with similar broad demographic characteristics in an inner city area of Lahore. The primary outcome measures for the trial is teachers’ mental health literacy. It will be assessed by using the previously applied (during WHO training of Master Trainers) self-administered questionnaire in both groups pre and post training and at 3 months’ follow-up. Secondary outcomes include: for teachers: Teachers’ self-efficacy (assessed by the Teachers’ Sense of Self Efficacy Scale (TSES) short form.); for students (11–16 years): socio-emotional skills and psychological problems measured by the Strengths and Difficulties Questionnaire (assessed at baseline and 3 months post intervention); for schools: the WHO School Psychosocial Profile Questionnaire (baseline and 3 months post intervention).

**Discussion:**

Given the high prevalence of child mental health problems, stigma and lack of services, it is important to consider alternate avenues for promoting positive mental health among youth. This pilot study should establish the effectiveness of the WHO-EMRO School Mental Health Manual-based Intervention improving teacher’s mental health literacy and helping them to learn practical steps that can be implemented at low cost in school settings. It will also provide information regarding intervention implementation and sustainability.

**Trial registration:**

ClinicalTrials.gov, ID: NCT02937714. Registered on 18 October 2016.

**Electronic supplementary material:**

The online version of this article (10.1186/s13063-018-2679-3) contains supplementary material, which is available to authorized users.

## Background

Pakistan is the sixth most populous country of the world with population over 188 million [1]. Almost 35% of population is under the age of 14 years [1]. Child and adolescent mental health thus needs to be considered and emphasized as an integral component of overall health and growth of this young population. The high prevalence of emotional and behavioral problems [2, 3] along with stigma of psychiatric problems and limited child and adolescent mental health services in the country, makes schools a natural platform for mental health promotion. The World Health Organization (WHO) also identifies the promotion of emotional health and well-being as a core feature of their health-promoting school initiative [4]. Schools can play an important role in promoting positive mental health, reducing stigma, raising awareness among teachers, parents and children about mental health issues as well as identifying and supporting youth experiencing mental health difficulties.

Teachers’ role in the school mental health initiatives cannot be overemphasized. Teachers’ own knowledge and beliefs regarding mental health influence the way that they respond to students’ mental health crises [5]. Studies suggest that teachers feel overwhelmed and incompetent to address mental health needs of their student due to their incompetence and lack of knowledge and skills in this area [6, 7]. Teachers’ education is identified as an effective mental health intervention in school settings promoting positive mental health and a sense of connectedness among stakeholders and facilitating student learning, thus improving the overall school atmosphere. Educational interventions involving teachers have shown significant improvement in teachers’ knowledge and attitudes regarding mental health and better accuracy of teacher identification of children and adolescents with mental health problems [8]. Knowledge improvement, reduction of stigma, and confidence in providing support to students as well as indirect positive effects on students were observed in a cluster randomized trial of mental health first-aid training of high school teachers [9]. Furthermore, mental health initiatives in schools help teachers to feel less stressed and be more satisfied with their role, and to save costs [10].

Although the importance of school for mental health promotion and early identification of mental health problems and teachers’ training in mental health has been evident for quite some time and has gained significant momentum in the West, it is almost non-existent in developing countries including Pakistan. Research from Pakistan on school mental health is very limited. In one study done in 1998 in rural Rawalpindi, a school-based programme succeeded in improving mental health awareness in school children, their parents, friends and neighbors; however, teachers’ awareness was not assessed [11]. Knowledge of school teachers regarding attention deficit hyperactivity disorder (ADHD) symptomatology improved in a teacher training programme for ADHD [12]. School mental health initiatives including steps to improve teacher’s mental health literacy, their professional development and training, encouraging teaching styles that promote mutual respect, and positive classroom strategies are almost non-existent in the country. Child mental health is considered a priority in the WHO’s Eastern Mediterranean Region (WHO-EMRO). Recognizing the need for wider implementation of evidence-based school mental health interventions in the region and to help in addressing the mental health literacy of educators in resource-constrained settings, a pilot study of a teachers’ training intervention based on the WHO-EMRO Manual of School Mental Health in Urban Lahore was planned [13]. Training aims for improving teacher’s mental health literacy and helping them to take practical steps that can be implemented at low costs in school settings. The intervention will be evaluated in a pilot randomized controlled trial (RCT), with teachers on a waitlist as the control group, to assess its effectiveness in improving teachers’ mental health literacy and self-efficacy in dealing with students’ mental health issues. It will also enable us to test the feasibility of key aspects of the trial design. The aim of this paper is to describe the study protocol of the pilot RCT.

### Aims and objectives of the study

This pilot RCT seeks to demonstrate the effectiveness of a teacher training programme based on the WHO-EMRO Manual of School Mental Health in improving teacher’s mental health literacy as compared to a waitlist control group. The secondary objective is to evaluate the effect of the WHO-EMRO School Mental Health Manual-based intervention in improving self-efficacy among school teachers. The study will also determine if mental health training of teachers may lead to an indirect improvement in a students’ outcome measure (emotional and behavioral difficulties) and the school psychosocial environment.

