### Participants and sample size

All the teachers in the participating schools of grades 1–10 of both genders will be approached. Exclusion criteria included lack of informed consent, teachers who are leaving/not planning to be in the school in 3 months’ time, and teachers who have not been involved in active teaching in last 6 months. Students of 11–16-years old studying in the participating schools whose parents will give informed consent will also be screened.

A sample size of 220 teachers (110 teachers each in the intervention and control groups) is estimated using 90% confidence interval, 5% absolute precision with expected percentage of improvement on mental health literacy in the intervention group as 10% and the control group as 1% [14].

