### Dissemination

A report will be prepared for each participating school containing the overall findings and also, from each school, anonymised results from the teacher and student questionnaire. Papers reporting the outcomes will be published in peer-reviewed journals. If the findings show the intervention to be effective, it will help in refining the large-scale RCT and the results will be disseminated to policy-makers in the private and Government sectors for this training to be included in mandatory teacher training.

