The aim of this paper is to describe the protocol of a RCT regarding an intervention programme designed to improve teachers’ knowledge, attitude and skills to promote children’s socio-emotional well-being and mental health in the school context in Pakistan. The presented intervention is based on the WHO-EMRO School Mental Health Manual. Specifically, the aim of this pilot RCT is to provide more information on adapting evidence methods for diverse cultures and related school settings. We are not aware of any previous RCT done in Pakistan focusing on teacher training in a whole-school approach. A particular strength of the study is its focus on secondary student’s outcome as well. The limited time available for the study makes the follow-up time of 3 months more feasible rather than 6 months, which might have been more appropriate to observe any significant change. Another limitation of the trial is the generalizability of the results to the Government sector and to elite private schools, which differ significantly in various socio-demographic variables and will not be targeted in this pilot trial. Contamination between teachers in the intervention and control groups may occur when recruiting teachers within the same school and is a limitation of the trial. Findings including the effectiveness and implications from this study will provide information supporting the large-scale RCT for training teachers to increase their mental health literacy and thus potentially improving future school mental health services. In addition, the trial will provide important information about any implementation issues and the extent to which it is likely to be sustainable in different settings in the country. Positive trends result from this trial will hopefully support the urgent work needed in school mental health in Pakistan.

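### Student and school outcomes are measured with about half of the consenting teachers trained and no untrained schools, so the trial cannot determine an indirect effect in either direction

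*Protocol article*

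**What the plan says.** Under Aims and objectives of the study, after the teacher objectives, the article states: "The study will also determine if mental health training of teachers may lead to an indirect improvement". The outcomes meant are students' emotional and behavioural difficulties and the school psychosocial environment.

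The design behind that aim is spread over several sections:

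- **Participants and sample size:** "A sample size of 220 teachers (110 teachers each in the intervention and control groups"). Teachers of grades 1 to 10 are approached. Students aged 11 to 16 with parental consent are screened.
- **Study design and Randomization:** willing teachers in consenting schools are allocated individually by computer-generated random numbers from the schools' teacher lists. Stratification by school is not mentioned. The waitlist arm gets no training during the study.
- **Outcome measures:** the SDQ and the school profile are taken at baseline and at 3 months.
- **Statistical analysis:** student and school measures are compared between baseline and follow-up with a t test.
- **Discussion:** the authors know of no earlier Pakistani RCT "focusing on teacher training in a whole-school approach". They concede that "Contamination between teachers in the intervention and control groups may occur when recruiting teachers within the same school", and that 6 months is a follow-up "which might have been more appropriate to observe any significant change". They call the student outcome a particular strength.
- **Dissemination:** if the intervention is found effective, results go to policy-makers "for this training to be included in mandatory teacher training".

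**The concern.** The unit that is randomised (the teacher) is not the unit on which these outcomes are measured (students across the school, and the school itself). With both arms inside every school, no school is fully trained and none is fully untrained. What is observed is the course of a school in which some teachers were trained. The aim, the whole-school framing and the policy use all concern something else: the effect of training a school's teachers.

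The interpretation of the result is at stake in both directions. A flat SDQ or profile could reflect low coverage or short follow-up. An improvement could reflect time or other influences, because no untrained schools are followed alongside. Either figure could also be carried into the large-scale RCT as if it described a fully trained school.

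**Working it through.** **1. The plan's own figure.** The inputs under Participants and sample size are "90% confidence interval, 5% absolute precision" and "expected percentage of improvement on mental health literacy in the intervention group as 10% and the control group as 1"%. The precision formula for a difference of two proportions gives

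n = 1.645² × [0.10 × 0.90 + 0.01 × 0.99] / 0.05² = 2.706 × 0.0999 / 0.0025 = 108.1,

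so 109 per group and 218 in total, against the stated 110 and 220. The figure reproduces. It rests on teacher literacy alone, and the article gives no sample-size basis for the student or school outcomes.

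**2. Coverage overall.** Trained share of randomised teachers = 110 / 220 = 50%. As a share of all staff it is 0.5 × consent share. The article gives no consent rate. Assumed rates of 100%, 80% and 60% give 50%, 40% and 30%.

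**3. Coverage by school.** The 1:1 split is fixed overall, not within each school. A simulation drew 110 of 220 teachers at random, with equal school sizes assumed and no stratification. The article expects five to six schools in one section and seven in another.

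| Schools | Average lowest trained share | Average highest trained share |
|---|---|---|
| 5 | 41% | 59% |
| 6 | 40% | 60% |
| 7 | 38% | 62% |

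In each case the chance that at least one school has more than half of its randomised teachers trained exceeds 99.9%.

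**4. What partial coverage could do.** Assume that the student or school effect is proportional to coverage f, with no spillover. For a comparison with 80% power at full coverage and two-sided 5% significance,

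power = Φ(f × (0.842 + 1.960) − 1.960), and the sample needed rises by 1 / f².

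| Coverage f | Effect retained | Power | Sample multiple |
|---|---|---|---|
| 0.50 | 50% | 29% | 4.0 |
| 0.40 | 40% | 20% | 6.3 |
| 0.30 | 30% | 13% | 11.1 |

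The first row needs only the 1:1 ratio and proportionality. The other rows also need the assumed consent rates.

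**5. The comparison itself.** Students are not tied to an arm, and every school is expected to hold both arms. A baseline-to-follow-up t test therefore has no concurrent untrained group. Control schools would remove that gap but not the partial coverage, and full coverage without control schools would leave the gap. The two limits are separate, and both apply.

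**The case against.** The strongest replies are these.

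- **Spillover.** The contamination that the Discussion concedes would raise effective exposure for students and schools, and so offset some dilution. This stands. The 29% ignores it, and the article describes no measurement of it.
- **Relevant teachers.** A student's exposure depends on who teaches that student. Study design describes the students as taught by the participating teachers, while Participants and sample size takes them from the participating schools. On the narrower wording, decliners need not dilute the SDQ result, and a share of all grade 1 to 10 staff includes primary teachers who may not teach these students. This stands, and is why a share among teachers of secondary classes is also needed.
- **Already disclosed.** The 3-month limit is conceded with its reason, so it is no new defect. Refusals will be reported under CONSORT. Partial coverage, however, is not named.
- **Modest aim.** The aim comes after the teacher objectives and is hedged by speaking of what training may lead to. The verb 'determine' still promises an answer.
- **Generic figures.** The article gives no student numbers, effect size or power for these outcomes, so the 29% illustrates scale and is not this trial's power.

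A reader might go further and infer that at most half of the teachers in each school are trained. The documents set no such cap, and step 3 shows that some schools will very probably exceed half. A reader might also infer that a null will be misread as no effect, or that the error runs only towards a null. The article does not say how a null would be read, makes policy use conditional on effectiveness, and does not name the SDQ or profile change as the planning effect for the larger trial. With an uncontrolled before-after comparison, a spurious improvement is just as possible.

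**Conclusion.** The point holds in this form: the student and school measures reflect about half of the consenting teachers trained, unevenly across schools, at 3 months and without untrained comparison schools. The aim claims more than that design can show, whichever way the result falls, and the trial does not test a whole-school approach. The 50% overall follows from the stated allocation. The halved effect and the fall from 80% to about 29% power rest on proportionality and no spillover, and the lower rows also rest on assumed consent rates. The primary teacher-literacy comparison is not affected by this point.

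**What to change.** 1. **Aims and objectives of the study:** replace 'determine if' with wording that the study will describe, as an exploratory outcome, the change in student and school measures from baseline to 3 months at about half teacher coverage. Calling it an estimate of the effect would still promise too much without a control.
2. **Discussion:** drop the whole-school description of this trial, and add partial coverage to the limitations beside follow-up and contamination.
3. **Statistical analysis:** report for each school the trained share of teachers, overall and among those teaching secondary classes, beside its SDQ and profile results.
4. **Interpretation:** state that neither a null nor a positive change will be read as the effect of training a whole school, or used unscaled to plan the large-scale RCT.

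The cost is small: wording, plus two percentages per school. The schools' teacher lists are already supplied for randomisation, and classes taught are already collected from participants. For teachers who decline, the schools would have to supply classes taught if the lists do not show them. No redesign is needed, so the change can be made with the trial underway. The downside is a weaker stated claim for these outcomes.

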## Methods

### Study setting

The study setting is private schools located in urban Lahore, having monthly fee structure of less than 3000 Pakistani rupees and matching in broad characteristics like student:teacher ratio, facilities, etc. Seven schools, from inner city areas of Lahore, are likely to be involved in the study in order to achieve the needed sample size.

### Participants and sample size

All the teachers in the participating schools of grades 1–10 of both genders will be approached. Exclusion criteria included lack of informed consent, teachers who are leaving/not planning to be in the school in 3 months’ time, and teachers who have not been involved in active teaching in last 6 months. Students of 11–16-years old studying in the participating schools whose parents will give informed consent will also be screened.

A sample size of 220 teachers (110 teachers each in the intervention and control groups) is estimated using 90% confidence interval, 5% absolute precision with expected percentage of improvement on mental health literacy in the intervention group as 10% and the control group as 1% [14].

### Study design

The study is a two-arm RCT. We expect to include five to six schools to obtain the required sample size. Schools will be sent a letter inviting them to participate. All the teachers in the consenting schools, who are willing to participate, will be recruited for the study. Participants will be randomly allocated to the intervention group (receiving the school mental health intervention during the study) or the waitlist control group (teachers who will not receive any training during the study period) using computer-generated random numbers. In order to evaluate the effectiveness of training, a pre- and post-study design will be used (see the Standard Protocol Items: Recommendations for Interventional Trials (SPIRIT) Diagram in Fig. 1). Participants’ mental health literacy and self-efficacy will be evaluated using questionnaires pre and post training and at 3 months’ follow-up. Students (11–16 years old) taught by these teachers and the school psychosocial environment will also be screened at baseline and 3 months after the intervention using the self-reported SDQ. The study follows the Consolidated Standards of Reporting Trials (CONSORT) Guidelines for the design and implementation of RCTs [15].

**Fig. 1 Fig1:**
[figure not shown]
Standard Protocol Items: Recommendations for Interventional Trials (SPIRIT) Diagram

Additional file 1 shows details of the SPIRIT Checklist items to be addressed in the clinical trial in more detail.

### Intervention

The intervention group will receive a training workshop based on a local adaptation of the WHO-EMRO School Mental Health Manual. The training was adapted in light of in-depth interviews by teachers and school administrators and discussions with relevant stakeholders to make it suitable for the Pakistani school system. The training will be three 6-h sessions delivered face-to-face over a 2-week period. Teachers can decline to participate or withdraw at any stage. Topics to be covered in training workshop are given in Table 1.

**Table 1 Tab1:** Summary of the modules in the World Health Organization, Eastern Mediterranean Region (WHO-EMRO) School Mental Health Manual

Module	Description
Module 1. Social-Emotional Childhood Development	• Developmental tasks of primary-school-age children (6–12 years) • Developmental tasks of secondary-school-age children (12–18 years) • Moral development • Brain development and implications for schooling
Module 2. Mental Health Promoting Schools (Promotion and Prevention)	• Core values of a mental health promoting school • The role of parents in their children’s education • Behavioral management strategies for schools Discipline and management of disruptive behavior Counseling Circle time • Physical health promoting efforts that impact mental health Nutrition Vision/ hearing/ speech Physical exercise • Media and mental health Screen time Internet addiction Cyberbullying • Suicide prevention
Module 3. Addressing Student Mental Health Problems in Your Classroom (and when to refer for additional help)	• Recognizing warning signs for different disorders: Depression Anxiety Pervasive developmental disorders Attention disorders Psychotic disorders Specific learning disorders Intellectual disability Conduct disorders Substance abuse • When to refer to a specialist for evaluation and treatment

The workshop will be conducted by the principal investigator (PI) along with one to two assistants (psychologists trained by the PI). The PI was trained over a period of 2 days by one of the WHO trainers and a Master Trainer of school mental health. ([name]). Participants will be provided with standardized school mental health manual handouts.

